#### Blinding

This trial is an open-blinding trial, because patients are usually unconscious and the packaging of the two trial drugs (BRS and LRS) differs significantly.

### Study procedures

#### Screening procedures

Investigators will use eligibility criteria to identify eligible adults with THS as soon as possible after the patient arrives at the hospital. If the patient meets the criteria for enrollment, the investigator will ask the patient’s legal representative for informed consent to participate in the trial. The screening diary is completed every 2 weeks, and the record investigator will record all patients deemed eligible for the trial. The log will include age, gender, inclusion/exclusion criteria, and other reasons for failure to enter the study arm. The screening log data will be reviewed regularly.

#### Randomization procedure

Enrolled patients will be assigned to the study arm in a 1:1 ratio based on the size of the assigned numbers via a computer-generated random number table within 10 min of admission. Before the study began, a random envelope was prepared for each bed. The envelope contains a card printed with a number (from the random number table). Once the patient is confirmed eligible to participate in the study and informed consent is obtained, the envelope will be opened and unblinding by the investigator immediately after the patient arrives at the bedside. Patient study arm is determined based on the size of the numbers on the card to ensure there is no delay in treating the patient. The investigator will not know the study arm until unblinding takes place and each envelope will be used only once.

#### Schedule of intervention

All patients will be managed according to the standard diagnosis and treatment process, regardless of whether they participate in the trial or not. After randomization, enrolled patients will receive intervention at the set time point, as showed in Fig. 2, and they will be followed up for 7 days.

#### Standard care

All patients are treated in accordance with the treatment of THS: Priority is relieving the life-threatening situation so that the injury can be preliminarily controlled, and then the follow-up treatment is carried out. The “saving life first, the protective function second, first emphasizing and then light, first urgent and then slow” [41] was followed. Damage-controlled resuscitation (DCR) strategy was adopted: immediately establish two or more venous channels, indwell the arterial sheath, perform ECG monitoring, and monitor the patient’s arterial blood pressure at the same time, implement permissible hypotension before major bleeding is controlled, and maintain SBP at 80–90 mmHg. Restrict the input of a large amount of liquid. Standard care includes:(A)Rapid assessment of injury(B)Continuous monitoring of vital signs(C)Control of bleeding(D)Respiratory support(E)Improvement and continuous follow-up of relevant laboratory and imaging examinations(F)Control of body temperature(G)Pain relief(H)Prevention and treatment of traumatic coagulopathy(I)Prevention and management of acidosis(J)The use of vasoactive drugs and positive inotropic drugs when necessary(K) Damage control surgery(L)Other symptomatic supportive treatment

#### Initiation of study care

When patients are enrolled in the trial, they will receive standard care and be resuscitated with fluids depending on the study arm. The first 6 h of resuscitation will be administered with BRS or LRS for early resuscitation only. After early resuscitation, the blood products will be given for resuscitation depending on the patient’s condition. Moreover, the patient’s blood sample will be collected before the fluid resuscitation. After the patient enters the study arm, only the fluid type corresponding to the study arm is used for resuscitation. Given that fluid is 500 ml/time, the administration speed is ≤ 10 ml/kg/h, and the total amount is less than 3L during the resuscitation for the first 6 h. Albumin can be used for resuscitation when necessary.

Enrolled patients will be block randomized to either study arm (Fig. 3 shows the drug application process).

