## Abstract

**Background:**

Traumatic hemorrhagic shock (THS) is the main cause of death in trauma patients with high mortality. Rapid control of the source of bleeding and early resuscitation are crucial to clinical treatment. Guidelines recommend isotonic crystal resuscitation when blood products are not immediately available. However, the selection of isotonic crystals has been controversial. Sodium bicarbonate Ringer solutions (BRS), containing sodium bicarbonate, electrolyte levels, and osmotic pressures closer to plasma, are ideal. Therefore, in this study, we will focus on the effects of BRS on the first 6 h of resuscitation, complications, and 7-day survival in patients with THS.

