## Introduction

### Background

Severe trauma is a major global public health problem, causing an estimated more than 5.8 million deaths worldwide each year, accounting for one in ten of all deaths [1]. Blood loss due to trauma is the most important cause of death and the leading cause of death among people under 40 years of age worldwide and can cause significant economic losses. Traumatic hemorrhagic shock (THS) refers to the pathophysiological process in which trauma leads to massive loss of effective circulating blood in patients, resulting in tissue hypoperfusion, cell metabolism disorder, and organ function damage [2]. In the early stages of trauma, control of bleeding prevents death, fluid resuscitation improves tissue perfusion, and prevention of traumatic coagulopathy (TIC) reduces secondary organ failure and ultimately minimizes mortality [3–10]. Based on the above, we found that the key to clinical treatment of THS patients is rapid control of the source of bleeding, early fluid resuscitation, and restoration of intravascular volume and oxygen carrying capacity [11]. However, the choice of optimal resuscitation fluid for THS patients is still a controversial issue. Finding fluid suitable for early resuscitation is a key problem that needs to be solved urgently in clinical treatment of THS patients.

Over the past decades, many clinical studies have confirmed that early fluid resuscitation using blood products is the best option. However, blood products are often difficult to obtain immediately in the early stages of trauma. Studies have shown that pre-hospital plasma use is not associated with survival benefits in rapid ground support [12, 13]. Hypertonic crystalloids, hypotonic crystalloids, and artificial colloids have significant component differences from plasma. Their use follows many risks, such as exacerbating acidosis, causing impairment of renal function, coagulation function, platelet function, and so on [14–29]. Therefore, they are not the most optimal option. Guidelines recommend using isotonic crystalloid resuscitation in cases where blood products are not immediately obtainable [1, 25, 30]. Studies show that isotonic crystalloids with similar components to plasma become the primary option for patients with THS, except for traumatic brain injury (TBI), and fluids with the potential to restore pH may be beneficial for resuscitation [24, 25, 27, 28, 31].

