## Methods

### Study design

This study is a clinical single-center, prospective, superiority, parallel-group, randomized controlled trial in patients with THS. The study will be conducted at the Department of Treatment Center for Traumatic Injuries and Emergency Intensive Care Unit (EICU) of the Third Affiliated Hospital of Southern Medical University, China. Patients who meet the eligibility criteria and obtain informed consent will be assigned to the test group or control group in a 1:1 ratio based on the size of the random number allocated to them. Patients will be resuscitated with the drug according to the study arm, and only this drug will be used for resuscitation in the early fluid resuscitation (6 h) period. Approval has been obtained from the Institutional Ethics Committee (IEC) of the Chinese Ethics Committee of Registering Clinical Trials. This study complies with the Declaration of Helsinki and the relevant regulations for clinical research in China. This trial has been registered as ChiCTR2100045044.

The protocol is written in accordance with the Standard Protocol Items: Recommendations for Interventional Trials (SPIRIT) guidelines, shown in Additional file 2. Figure 1 (study scheme) shows an overview of the study process. Figure 2 shows the schedule of enrolment, interventions, and assessments.

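### The first-hour stopping rule ends participation for patients already randomised in an open-label trial, and the text states no route to blood before 6 h

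*Protocol article*

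**What the plan says.** All references are to the protocol article.

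**Early stop.** Stopping criteria lists transfusion, an intervention or surgery in the first hour after admission. The same list contains early death, withdrawal at the patient's request, failure to complete the observation period, and a best-interest clause about continuing in the study. Randomization procedure places allocation within 10 min of admission. Blinding describes an open trial in which the two products look clearly different. Standard care includes control of bleeding and damage control surgery.

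**Blood before 6 h.** Study design says that "only this drug will be used for resuscitation in the early fluid resuscitation (6 h) period". Initiation of study care repeats this ("The first 6 h of resuscitation will be administered with BRS or LRS for early resuscitation only") and continues: "After early resuscitation, the blood products will be given for resuscitation", depending on the patient's condition. It names one exception: "Albumin can be used for resuscitation when necessary". Test group and Control group say that the study fluid goes on if shock persists.

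**Rationale.** Background says that "many clinical studies have confirmed that early fluid resuscitation using blood products is the best option", then adds that "blood products are often difficult to obtain immediately in the early stages of trauma". The abstract puts the condition this way: "Guidelines recommend isotonic crystal resuscitation when blood products are not immediately available". Schedule of intervention states: "All patients will be managed according to the standard diagnosis and treatment process, regardless of whether they participate in the trial or not".

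**The concern.** The stopping rule is triggered by treatment given almost entirely after randomisation. Whether a bleeding patient is transfused or taken to theatre in the first hour depends on severity, on early response to the fluid, and on the judgement of staff who know the arm. If participation ends on that decision, the patients who remain are no longer the groups that were randomised. Lactate clearance at 6 h and duration of shock both depend strongly on severity, so both can be affected. The rule also penalises care that the plan promises to everyone.

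The second matter is one of clarity and care. As worded, blood products come after the 6-h crystalloid period, and the text names no route for a patient still in shock during it. That sits badly with the article's own statement about early blood products. Transfusion between 1 h and 6 h is not a named reason to stop, yet it departs from the fluid rule, and the text does not say how it is handled.

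**Working it through.** **1. Share of the stopping window after randomisation.** The window is 60 min from admission (Stopping criteria) and allocation is at 10 min or earlier (Randomization procedure). 60 − 10 = at least 50 min.

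**2. What the rule ends.** The other entries in the list (withdrawal, incomplete observation, continuing in the study) concern participation and not only study drug. The natural reading is that the patient leaves the trial.

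**3. Whether the missing-data method repairs it.** Statistical analysis uses last observation carried forward, with multiple imputation as a sensitivity analysis. Lactate is measured at 0, 0.5, 1, 1.5, 3 and 6 h. A patient stopped in the first hour after admission has a value from about 1 h at the latest to carry to 6 h. If stopped before the 0.5 h sample, the baseline itself is carried and clearance is zero by construction. Duration of shock has no earlier value to carry. Standard multiple imputation assumes that the stop is explained by what was observed, which is doubtful for an arm-aware clinical decision.

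**4. The plan's own sample size.** Inputs from Sample size: one-sided alpha 0.025, power 0.80; lactate clearance 32% against 35%, SD 10; shock duration 3 h against 1.5 h, SD 4 h; 10% loss.

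n per arm = 2(1.960 + 0.842)² × SD²/diff²

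- Lactate: 174.4, so 175; the t-based value is 175.4, so 176 as stated. 176/0.9 = 195.6, so 196 per arm and 392 in total, as stated.
- Shock duration: 112; t-based 112.6, so 113 as stated. 113/0.9 = 125.6, so 126 per arm and 252 in total, as stated.

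The planned figures reproduce.

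**5. Margin if stopped patients were not analysed** (an assumption; the article does not say so). 200 − 176 = 24 per arm, and 24/200 = 12%, from all causes.

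Power = Φ(diff/SD × √(n/2) − 1.960), with assumed loss shares:

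| Loss | n per arm | Lactate | Shock duration |
|---|---|---|---|
| 0% | 200 | 0.851 | 0.963 |
| 10% | 180 | 0.812 | 0.945 |
| 12% | 176 | 0.804 | 0.940 |
| 20% | 160 | 0.765 | 0.918 |
| 30% | 140 | 0.709 | 0.881 |

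Each column is for one endpoint alone. Sample size requires both, so joint power cannot exceed the lactate column.

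**6. Price of allowing blood before 6 h.** Suppose 5% or 10% of each planned difference is lost (assumed), with 180 analysed per arm.

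- Lactate: a difference of 3.00 gives 0.812, 2.85 gives 0.771, 2.70 gives 0.726. The n for 80% power goes from 175 to 194 or 216 per arm.
- Shock duration: 0.945 becomes 0.922 or 0.893.

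**The case against.** **On the stop.** Stopping criteria does not say that stopped patients leave the primary analysis, and analysis sets commonly belong to an SAP that is not shown. Planning for imputation suggests that incomplete patients may be kept. This stands as far as it goes: exclusion from analysis is not established, and the loss shares above are assumed. It does not remove the point. Once participation ends at about 1 h, the 6-h lactate and the end of shock may never be observed, and no analysis set restores them.

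**On blood.** This case is stronger. A reader might infer that the trial withholds blood that is at hand from patients in shock. The documents do not support that as a finding. Nothing states that blood is barred when available; that is inferred from the absence of an availability condition. The figures, including the drug application process, are not shown and could hold a rescue route, and an article condenses the full protocol. The word *only* can be read as governing the type of crystalloid, and Resuscitation fluid and drug usage records blood products from study entry. The best-interest clause also offers a way out, although by ending participation.

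A reader might also see a three-way contradiction with the rationale, the standard-care promise and albumin. That goes too far. The Background is rationale and not a treatment rule, the standard-care list does not name transfusion, and albumin is an express exception.

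Lastly, one might calculate that a patient at the maximum rate reaches the 3 L cap before 6 h and is then left without fluid or blood. That needs assumed weights and the ceiling rate throughout, whereas the plan restricts volume and reassesses before each 500 ml. At an average of 500 ml/h or less, 3 L lasts the full 6 h. It is not evidence of harm.

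Holding co-interventions constant to isolate a crystalloid effect is a legitimate design aim, and the trial reports ethics approval. What remains is that the sequencing of blood after the 6-h period is in the text, and the text gives no exception for persistent shock.

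**Conclusion.** The early stop is a real defect and should be amended. It acts on randomised patients for at least 50 of its 60 min, on a decision made with knowledge of the arm, and partly on care that the plan calls standard. It can unbalance both primary endpoints; neither the size nor the direction can be derived from the article, because the frequency of early transfusion or surgery by arm is not given. The effect on power is secondary: a 12% margin on lactate, and 77% power at an assumed 20% loss if those patients went unanalysed.

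The rule on blood is a defect of wording with a possible clinical consequence. The plain text puts blood after 6 h and states no rescue route, which fits poorly with the Background. It does not establish that available blood will be withheld. This part rests on the text alone, without the figures or the full protocol.

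**What to change.** 1. Amend Stopping criteria so that early transfusion, intervention or surgery may change treatment but does not end follow-up or remove a randomised patient from the primary as-randomised analysis.
2. State in Study design and Initiation of study care that the restriction to BRS or LRS governs the choice of crystalloid, and that clinically indicated blood products may be given before 6 h on the same criteria in both arms.
3. Record whether each product was given before or after 6 h, report use by arm, and add one sensitivity analysis. Total volumes to day 7 are already collected.

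**Cost.** One amendment in a trial that has been recruiting since May 2021, one time field on the case report form, and one further analysis. The statistical price is possible dilution of the crystalloid contrast, as in step 6 of the working: lactate power at 180 per arm falls from 81% to about 77% or 73% under the assumed 5% or 10%. Keeping early-treated patients recovers part of it. At the upper limit, with all 200 per arm analysed, 0.285 × √100 − 1.960 = 0.890 gives 81%, and 0.270 × √100 − 1.960 = 0.740 gives 77%.

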**Fig. 3 Fig3:**
[figure not shown]
Drug application process

Clinical criteria of successful shock resuscitation include:(A)SBP was maintaining at 80–90 mmHg(B)Heart rate was less than or equal to 100 bpm/min(C)A pulse of the aorta was palpable(D)Increased cardiac output (greater than or equal to 4.0L/min)(E)Improved peripheral perfusion (ruddy and dry skin, capillary refilling time less than 2 s)(F)Mixed venous oxygen saturation is greater than or equal to 60% and arterial oxygen saturation greater than or equal to 80%(G)The urine volume was greater than that of 0.5 ml/(kg min)(H)Consciousness improvement(I)Lactate level ≤ 2 mmol/L

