##### Test group

For standard care, damage-controlled resuscitation strategy is used, only BRS during fluid resuscitation is used, 500 ml/time is used, dosing rate of ≤ 10 ml/kg/h is used, SBP at 80–90 mmHg is maintained, and the total amount is less than 3L during the resuscitation for the first 6 h. Investigators will evaluate whether the patient’s shock state is corrected before each administration. If the resuscitation is successful, the drug will be stopped, and if the shock persists, the drug will be continued.

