##### Control group

For standard care, damage-controlled resuscitation strategy is used, only LRS during fluid resuscitation is used, 500 ml/time is used, dosing rate of ≤ 10 ml/kg/h is used, SBP at 80–90 mmHg is maintained, and the total amount is less than 3L during the resuscitation for the first 6 h. Investigators will evaluate whether the patient’s shock state is corrected before each administration. If the resuscitation is successful, the drug will be stopped, and if the shock persists, the drug will be continued.

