#### Cessation of study care

For this study, successful shock resuscitation (end of study care) will be defined as the last intravenous injection of BRS /LRS investigator who evaluated the patient’s shock state and believed that shock resuscitation had achieved success.

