### Detailed outcome measures collected

#### Duration of shock

The time point at which the patient began in the shock state and the time point at which shock resuscitation was successful during the entire trial process will be recorded, and the shock duration will be calculated.

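### The end of the co-primary endpoint duration of shock is set by an open-label investigator's judgement, against a list of success criteria that cannot be applied as printed

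*Protocol article*

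**What the plan says.** Primary endpoint lists duration of shock and 6 h lactate clearance, and Sample size requires success on both. Under Duration of shock, the interval runs from the start of shock to "the time point at which shock resuscitation was successful during the entire trial process".

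Three places say how that end arises. Test group and Control group have investigators judge whether the patient's "shock state is corrected before each administration", and act on the answer: "If the resuscitation is successful, the drug will be stopped, and if the shock persists, the drug will be continued". Cessation of study care says that successful resuscitation "will be defined as the last intravenous injection of BRS /LRS", at the point where the investigator "believed that shock resuscitation had achieved success". The end is therefore a recordable time, but one fixed by a judgement. Blinding says "This trial is an open-blinding trial", and no blinded or independent assessor is named.

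Initiation of study care, directly after Fig. 3, gives nine items, A to I, introduced by "Clinical criteria of successful shock resuscitation include". Among them are systolic pressure held at 80–90 mmHg (A), improved consciousness (H), lactate at or below 2 mmol/L (I) and, as item G, "The urine volume was greater than that of 0.5 ml/(kg min", that is, per kilogram per minute. The visible text does not say whether all, any or a set number must hold. Table 1 does give such a rule for entry: history, the first group of signs, and three of the four signs in the second group.

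**The concern.** When the endpoint is the time at which somebody declares recovery, its validity depends on how tightly the declaration is tied to recorded facts. Here the person who declares it knows the arm, and the same declaration stops the study fluid. The list that should discipline the decision contains items that have to be set aside or reinterpreted, and the reader is not told which.

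Two patients with the same recorded state can then be given different end times. If staff tended to call success earlier in one arm, that tendency would pass straight into a co-primary endpoint. Because both primaries must be met, a weakness in either bears on the trial's claim.

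**Working it through.** **1. The plan's own figure.** Inputs from Sample size: 3 h against 1.5 h, SD 4 h, one-sided alpha 0.025, power 0.80. Per arm, n = 2 × (1.960 + 0.842)² × 4² / 1.5² = 112 after rounding up; the t-test version gives 112.6, so 113. Then 113 / 0.9 rounds up to 126 per arm, 252 in total. This reproduces the plan. The point is not about arithmetic.

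**2. Item G (urine).** 0.5 ml/kg/min × 60 = 30 ml/kg/h. Table 1 uses 0.5 ml/kg/h, so the ratio is 30 / 0.5 = 60. The maximum infusion rate is 10 ml/kg/h, so G asks for urine at 30 / 10 = 3 times the fastest permitted inflow of study fluid.

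**3. Item A (pressure).** 80–90 mmHg is a closed band. It repeats the treatment target, which Standard care applies only until major bleeding is under control. A patient who recovers to 110 mmHg fails it. Table 1 also admits a patient on a fall of at least 40 mmHg: from a baseline of 140, that patient enters at 140 − 40 = 100, already outside the band.

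**4. Item H (consciousness).** Table 1 needs three of four signs, and altered consciousness is only one of them. A patient with the skin, urine and pulse signs can enter alert and has nothing to improve. The Blinding section says patients are usually unconscious, so these are probably a minority.

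**5. Consequence of 2 to 4.** All nine items together cannot be the working rule as printed, and the visible text states no other.

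**6. What a shift would do (illustration; the shifts are assumptions).** With SD 4 h and 200 per arm, SE = 4 × √(2/200) = 0.40 h. With no true effect, the one-sided rejection rate is 1 − Φ(1.96 − shift/SE):

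| Average shift toward test arm | This endpoint | Both endpoints, if lactate differs as planned |
|---|---|---|
| none | 2.5% | 2.1% |
| 10 min | 6.1% | 5.2% |
| 15 min | 9.1% | 7.7% |
| 30 min | 23.9% | 20.3% |

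The last column multiplies by the lactate power at 200 per arm. There SE = 10 × √(2/200) = 1.0 point and power = 1 − Φ(1.96 − 3/1.0) = 0.851. It assumes independent tests. If lactate truly does not differ, the lactate test holds trial-level error at 2.5% or less, whatever the shift.

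**7. How plausible the shifts are.** Success is judged before each 500 ml. At an assumed 70 kg and the maximum rate, a bag lasts 500 / (10 × 70) h = 42.9 min. Shifts of 10, 15 and 30 min then need about 10/42.9 = 23%, 35% and 70% of test patients, net of control, to be called a whole bag early. At 50 kg a bag lasts 60 min and the shares are 17%, 25% and 50%. Slower infusion lowers them further.

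**8. Lactate as a success item.** Taking clearance as the proportional fall from baseline, the planned means of 32% and 35% bring lactate to 2 mmol/L by 6 h only from baselines up to 2/0.68 = 2.9 (control) or 2/0.65 = 3.1 (test) mmol/L. Whether item I is required therefore matters a good deal to the end time.

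**The case against.** The best defence has four parts.

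- **The rule may exist elsewhere.** Fig. 3 shows the drug application process, and under Test group and Control group that process is the success decision. The article also condenses a longer protocol. A reader might infer that no combination rule exists at all; the document does not support that, only that none is visible. A rule in either place would still not repair G or A, or the definition of success by belief.
- **G is a unit slip.** Anyone at the bedside would read it as ml/kg/h, in both arms alike. A reader might infer that G itself biases the comparison; it does not. It is an error in a decision threshold, and it forces an unwritten correction.
- **A and H are awkward for some patients only.** Systolic pressure is meant to stay at 80–90 mmHg during study fluid, and a clinician would count an alert patient as satisfying H. That is sensible practice, but it is not what the text says.
- **The error rates are hypothetical.** The document contains no evidence of any shift, and the 30 min case needs about 70% of 70 kg test patients called a bag early at the maximum rate. The trial-level figures also require lactate to improve as planned while shock duration does not change, with independent tests, although lactate is itself a success item. This stands: the table in the working shows sensitivity, not an estimate.

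**Conclusion.** The point holds in a limited form. The end of a co-primary endpoint rests on an open-label investigator's belief, and items G, A and H of the list meant to guide it cannot be applied as printed: G for every patient, A for those above 90 mmHg, H for those who enter alert. No combination rule is visible.

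The size of any resulting bias cannot be derived from the document. Average shifts of 10 or 15 min would take this endpoint's false-positive rate to about 6% or 9%, given SD 4 h and 200 per arm, but those shifts are assumptions. A reader might infer that the trial's overall false-positive rate is inflated. The document does not support that as a general statement, because the lactate co-primary caps the rate at 2.5% when lactate does not differ. Nor is the sample size in question. This is a definition worth repairing before analysis, not a demonstration that the endpoint is biased.

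**What to change.** 1. Correct G to 0.5 ml/kg/h.
2. Make A a floor: systolic pressure at or above 80 mmHg, sustained.
3. Count H as met when consciousness was normal at entry.
4. For the primary analysis, derive the end of shock in both arms by one fixed rule from recorded values at the existing evaluations (before each bag and at the scheduled assessments), not from the investigator's belief. The decision to stop fluid stays with the treating team.
5. The sponsor should choose the items in the rule, preferring objective ones, and state how they combine. The rule should not already be satisfied at entry. The pressure floor alone would be, for a patient admitted at 100 mmHg after a fall from 140.
6. Analyse the endpoint with and without lactate at or below 2 mmol/L. Lactate is both a listed success criterion and the other co-primary, and the control fluid supplies it.

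The direct cost is protocol and analysis-plan wording and a line on the case report form for each evaluation. There are downsides. The derived end may differ from the time study fluid stops, and it is only as fine as the evaluations, about 43 min apart at best for 70 kg before each bag. Some items may be unrecorded for patients enrolled since May 2021. Items such as capillary refill would still be read by unblinded staff. The pilot values behind the sample size (3 h, 1.5 h, SD 4 h) need rechecking under the fixed rule.
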